### Health economic evaluation

Health economic evaluation will be made from a societal perspective. The types of resources included in the analysis will be based on a review by Kidholm and Kristensen (62) and include:

Program costs:

○ Fixed costs: Hardware and software, training of the psychologists,○ Variable costs: Number of consultations and duration of consultations.

Economic consequences:

○ Sick leave (absence from study or work)○ Changes in labor market attachment○ Contacts to GP, psychologist, hospital, emergency ward○ Participants time when doing homework assignments.

Except for the fixed costs, data will be collected from the participant and from health registers (the Danish National Patient Register, National Health Insurance Service Register). Reporting of the study will follow the CHEERS guideline by Husereau, Drummond (63).

### Monitoring

Since the trial has a short duration and presents a minimal risks to the participants, no interim analysis is planned, and no data monitoring committee will be assigned. Cybersickness similar to motion sickness may occur in the VR-setting. The VR-exposure scenarios are designed in a way to minimize cybersickness, and the exposure sessions are brief which also diminishes the risk of experiencing cybersickness. Cybersickness will be monitored using the Simulator Sickness Questionnaire. Adverse events will be registered by the therapists after each therapy session.

### Ancillary and post trail care

Participants that are enrolled into the study are covered by indemnity for negligent harm through The Patient Compensation Association (Patienterstatningen). There may be a burden associated with answering questionnaires. In order to increase motivation and acknowledge efforts to answer questionnaires for research use, the participants are rewarded with a gift card worth 500 DKK after treatment. This is only rewarded when the participant completes the treatment and is taxable.

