**Methods:**

The trial is a randomized controlled, assessor-blinded, parallel-group superiority trail. The study has two arms: (1) CBT including exposure *in vivo* (CBT-Exp), (2) CBT including exposure therapy using individually tailored VR-content and a system to track anxiety levels (CBT-ExpVR). Treatment is individual, manual-based and consists of 10 weekly sessions with a duration of 60 min. The study includes 90 participants diagnosed with SAD. Assessments are carried out pre-treatment, mid-treatment and at follow-up (6 and 12 months). The primary outcome is the mean score on the Social Interaction Anxiety Scale (SIAS) with the primary endpoint being post-treatment.

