#### Secondary hypotheses

At 6 and 12 months follow-up, we expect that VR-treatment will result in lower levels of social anxiety than *in vivo*-treatment.Post treatment and at 6 and 12 months follow up we expect that VR-treatment will result in lower levels of depression and higher levels of self-rated health than *in vivo*-treatment.The dropout rate we expect will be lower for the VR-treatment compared to the *in vivo*-treatment.

In addition to the evaluation of effect, a health economic evaluation will be made from a societal perspective.

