### Statistical analyses

The primary statistical analysis will be carried out as intention to treat (ITT). We will use linear mixed models to analyze the data. Separate analysis will be performed for each outcome variable. A two-level model with observations nested within participants is used. The fixed effects will be time, intervention, and the interaction between time and intervention as well as the baseline score. In addition to the primary analysis, a per-protocol analysis will be carried out on those participants completing at least 50% of the exposure sessions, interpreting the results cautiously due to the potential selection bias and confounding. Linear mixed models produce accurate estimates under the assumption that data are missing at random (MAR). A sensitivity analysis will be carried out where missing data will be handled by multiple imputation (m=100). Imputations will be based on baseline characteristics and secondary outcomes used chained equations. The moderating effect of the working alliance, depressive symptoms, alcohol, and drug use on the treatment outcome will be explored as subgroup analysis with continuous moderators by including them as covariates interacting with treatment and time. Model validation in the linear mixed model will be performed by inspection of qq-plots of residuals and best linear unbiased predictors to assess normality, and plotting residuals against fitted values to check homoscedasticity. If assumptions are violated, analysis will be performed after log-transformation. If assumptions do not hold under log-scale, bootstrapping will be applied with the linear mixed model, taking bootstrap sampling clustered by participant, and estimating post-treatment effect using bias-corrected accelerated confidence intervals (61).

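### The gift card meant to reward answering questionnaires is paid only for completing treatment, which adds an avoidable risk of informative missing data at the primary endpoint.

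*Protocol article*

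**What the plan says.** The section *Ancillary and post trail care* gives the purpose of the payment: "In order to increase motivation and acknowledge efforts to answer questionnaires for research use, the participants are rewarded with a gift card worth 500 DKK". It then gives the condition: "This is only rewarded when the participant completes the treatment and is taxable". Purpose and condition refer to different behaviours.

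Four other parts of the article bear on this rule:

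- **Endpoint.** The abstract states: "The primary outcome is the mean score on the Social Interaction Anxiety Scale (SIAS) with the primary endpoint being post-treatment". *Data collection and management* puts that assessment at week 10, after a mid-treatment assessment at week 5.
- **Analysis.** *Statistical analyses* states: "The primary statistical analysis will be carried out as intention to treat (ITT"). On missing data it says: "Linear mixed models produce accurate estimates under the assumption that data are missing at random (MAR"), and adds: "A sensitivity analysis will be carried out where missing data will be handled by multiple imputation (m=100"). The imputations draw on baseline characteristics and secondary outcomes.
- **Leaving treatment.** *Criteria for discontinuing allocated intervention* removes from treatment anyone with more than three missed appointments. It does not remove them from assessment.
- **Expected dropout.** *Secondary hypotheses* states: "The dropout rate we expect will be lower for the VR-treatment", compared with the in vivo arm. *Sample size* allows for 20% dropout in a total of 90.

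**The concern.** An intention-to-treat comparison at week 10 depends on SIAS scores from people who stopped treatment as well as from those who finished. The payment rule withdraws the reward from exactly the first group, although its declared aim is questionnaire response. Any missing SIAS that results would be concentrated among those who discontinue, and the protocol itself predicts that their number differs by arm.

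The planned methods give limited protection. The mixed model and the multiple imputation, as described, assume that missing scores can be predicted from observed data. If people who stop and do not respond are worse (or better) at week 10 than their earlier scores suggest, neither method corrects for it. Obtaining the scores is the direct protection, and the payment rule works against it.

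**Working it through.** **1. The plan's own sample size.** Inputs from *Sample size*: drops of 10 and 20 points, so a difference of 10; SD 15; significance level 0.05 (two-sided assumed, since the section does not say); power 0.80.

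- n per arm = 2 × (1.960 + 0.842)² × 15² / 10² = 35.3, so 36. The plan states 35.
- Power at 35 per arm is 0.796 by the normal approximation and 0.785 by the t-test. The plan states 0.80.
- Allowance for dropout: 70 / 0.80 = 87.5, so 88. The plan states 90.
- At 20% loss, 90 × 0.80 = 72 remain, or 36 per arm. Power is then 0.807 (normal) or 0.797 (t-test).

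The figures reproduce within rounding. A 20% loss is already budgeted for, so the point does not rest on power.

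**2. How many participants the rule touches.** If the planned 20% is read as treatment dropout, 0.20 × 90 = 18 participants forfeit the card. The article does not say how many of these would fail to return the week-10 SIAS, or how many more would return it if paid, so no recovery rate is claimed.

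**3. What informative missingness could do.** Let p be the proportion in an arm without a week-10 SIAS, and let G be the number of points by which their mean is worse (higher) than that of the observed participants. The full intention-to-treat mean in an arm is the observed mean + p × G. For the contrast VR minus in vivo:

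observed-only contrast − full contrast = (p in vivo − p VR) × G

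The document gives neither arm-specific p nor G. All the values below are assumptions, and they take every dropout as unobserved at week 10.

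| p VR | p in vivo | G = 5 | G = 10 | G = 15 |
|---|---|---|---|---|
| 20% | 20% | 0 | 0 | 0 |
| 15% | 25% | 0.5 | 1.0 | 1.5 |
| 10% | 30% | 1.0 | 2.0 | 3.0 |

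With unequal dropout the range is 0.5 to 3 points, which is 0.5/10 = 5% to 3/10 = 30% of the planned 10-point difference. The upper end needs a threefold ratio of dropout and a deficit of one full SD.

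**4. Direction.** A VR benefit is a negative contrast. With more dropout in vivo and worse unobserved scores, the shift is positive, so the VR benefit is understated. If the unobserved participants were instead better than the observed, the sign would reverse.

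**5. What the model removes.** The table is for an observed-only comparison. The planned model includes the baseline score and can use an available week-5 score, so only the part of G that these do not explain remains.

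**The case against.** The strongest reply is that losing a gift card is not losing an assessment. The outcome schedule is not limited to completers, the missed-appointment rule ends treatment only, and *Randomization and blinding* has a blinded clinician administer the pre-, mid- and post-test, so there is another route to the week-10 score. All of this stands. A reader might infer that people who stop treatment are not followed, or that they are told they will get nothing for answering. The article says neither: the participant information is not shown, and completion of treatment is not defined there. Nor can an article that condenses a fuller protocol be faulted for not spelling out follow-up of those who leave.

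A second reply is that a payment for completion may itself keep people in treatment and so reduce missing data. That is possible, and it is a real cost of moving the condition. The declared purpose, however, is questionnaire response, and the intention-to-treat analysis needs scores from leavers whatever their number.

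A third is that the card is the same in both arms. This also stands. A reader might infer that the payment biases the comparison of dropout rates, but an equal payment creates no direct difference between arms. It may lower dropout overall, and the document offers no way to say that it distorts the contrast.

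Finally, the sizes rest on assumed inputs before model adjustment. That is correct, which is why they are given as a range that includes zero.

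What survives is narrow: the article states the rule outright, the rule does not match its own purpose, and it makes missing week-10 data more likely in the group where missingness is most likely to be informative.

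**Conclusion.** The point holds as a cheap improvement to the design; no bias has been demonstrated. The mismatch between the purpose and the condition of the payment is explicit in the text. Its effect on the primary result cannot be computed from the document. The illustration runs from 0 to 3 SIAS points before adjustment, under assumed dropout splits and deficits, with baseline and week-5 scores absorbing part of it.

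Two stronger conclusions may tempt a reader and are not supported. The trial is not underpowered on this account, since the planned power is met at 20% loss. The rule also does not point towards a false positive: with dropout as the protocol expects and worse unobserved scores, it would work against the superiority hypothesis.

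**What to change.** Pay the gift card on completion of the post-treatment questionnaire, regardless of the number of sessions attended, and amend the participant information to match. No treatment rule, endpoint or analysis changes.

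The cost at the planned 20% dropout is at most 18 × 500 = 9,000 DKK, reached if all 18 respond. It rises with dropout; at an assumed 30% it would be 27 × 500 = 13,500 DKK. The ethics committee would need to be notified. The trial would also give up a possible inducement to finish treatment, which should be weighed openly when the change is made.

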### Dissemination policy

Results will be disseminated regardless of the magnitude or direction of effect. Both positive, negative, and inconclusive results will be made public and both beneficial and harmful effects of adaptive virtual reality exposure therapy will be reported. Dissemination will happen in scientific journals, at scientific conferences, as well as via www.clinicaltrials.gov. Authorship will be determined according to the Vancouver Guidelines. Recruitment will start in March 2022. Treatment will be carried out during 2022 and until the spring of 2023. Follow-up will be finished spring 2024. A report on trial results will be submitted in 2023. In addition, the results will be made public via the press, the webpage of the Center of Digital Psychiatry and social media.

## Discussion

The study described in this protocol will assess the efficacy of adaptive VR-exposure applied in a CBT framework. The effect of adaptive virtual scenarios utilizing psychophysiological measures to estimate anxiety levels in therapy remains unexplored (31). The study is a randomized controlled trial with a large sample size that includes follow-up data and validated measures for social anxiety outcomes. The present study will add to the existing knowledge on VR-exposure used in therapy. The project will be of great importance if it confirms that the treatment is suitable for individuals with SAD. Very few individuals with SAD end up ever seeking treatment. For this individual with SAD, VR-reality interventions might lower the threshold for seeking treatment. We need different treatment options and more effective treatments, which is particularly important, because SAD starts out at a young age with recovery taking decades to occur.

Concerning practical and operational issues involved in performing the study, we know from previous research that recruiting participants for SAD can be challenging. Based on our experience we have developed a deliberate plan for recruitment. Halfway through the recruitment period (June 2022), we will evaluate our progress and make adjustments to the recruitment procedures if needed.

## Ethics statement

This study has been approved by the Medical Research Ethics Committees in Denmark, *de Videnskabsetiske Medicinske Komiteer* (Case number: 2170848). Important protocol modifications will be communicated to the Medical Research Ethics Committees. Participants receive oral and written information before they are asked to give their written informed consent to participate in the study.

